### Intervention

Shortly before the tools are activated in participating CHCs, clinic staff members will be oriented to the CDS tools by an OCHIN EHR trainer (either on-site or remotely). Clinic staff will be offered a series of structured, sequenced activities using training materials developed by the study team in collaboration with the trainer. This will be the only form of implementation support offered to the main trial clinics as we seek to assess the adoption and impact of the CDS tools in a real-world situation.

### Analytic Framework

Mixed methods will be used to assess tool adoption and impact within a realist framework designed to identify what works, for whom, and in what circumstances [42,43]. The realist approach focuses on the context-dependent causal pathways through which an intervention (here, the CDS tool) produces outcomes (here, primarily adaptation of care plans based on patient-specific social risks and improved CQMs; Figure 3).

**Figure 3 figure3:**
[figure not shown]
Realist evaluation framework. Resources: the resource or resources offered by the program under study. Context: pre-existing individual, social, institutional, economic and system-level values, norms, and relationships in which interventions are introduced. Reasoning: reasoning and reaction of stakeholders in response to resource or resources. Outcomes: intended and unintended changes resulting from the intervention. CHC: community health center; CQM: clinical quality measure; EHR: electronic health record; PCP: primary care provider; SDH: social determinants of health.

#### Data

All quantitative data will be extracted from OCHIN’s Epic EHR; these data are centrally managed and quality checked [44-46]. Qualitative data for the intervention phase will be collected via semistructured interviews with diverse clinic staff who interface with the CDS tools during patient care (eg, providers, care managers, and medical assistants) and an EHR-embedded provider card study at each study site. The interviews will explore relevant clinical contexts, perceptions and use of social risk data and CDS tools in clinical encounters, and the impact of patient-reported social risk data on clinical decision-making, quality of care, and patient-provider interactions, including potential negative impacts of tool use. Card studies are short (<1 minute) surveys designed to obtain point-of-care data on clinical decision-making [47]. This card study, which will be embedded within the EHR and, therefore, the provider workflow, will be used to assess provider reactions to and actions taken based on patient-reported social risk data.

#### Quantitative Analyses

We will describe the percentage of clinic encounters at which (1) the CDS tools appeared to users at the intervention clinics, (2) users reviewed tool suggestions, and (3) the suggested care plan adaptations were enacted.

The primary trial outcomes are changes in the two CQMs expected to be affected by social risk–informed care: blood pressure control and HbA_1c_ control. Each CQM’s denominator will be defined according to which patients are eligible for that measure at the time of a clinic visit (eg, patients with diabetes are in the HbA_1c_ measure denominator) per national CQM measurement specifications [41]. Two-level hierarchical linear models [48-50] will be used to assess the impact of CDS tools on these outcomes. As these outcomes are binary, the generalized form of the hierarchical linear model with a log link and binomial distribution will be used. Textbox 1 shows other potential covariates; this list will be finalized based on the extent to which person-level covariates were balanced between the final intervention and control arms and will be included in the first level of the model representing the person level. The second level of the model, the CHC level, will include arm as an independent variable (control vs intervention) and a random effect for the intercept (ie, intercept-as-outcomes model). Population-averaged marginal proportions and associated 95% CIs will be calculated by arm, along with the difference between those proportions (ie, the marginal effect) and the associated 95% CI that incorporates the random effects (ie, differences between CHCs) and any included covariates.

In secondary analyses, a repeated cross-sectional design will be used to assess the differential changes in the outcomes across time. A panel design is impractical in this population of CHC patients, so using repeated measures would result in a selective (eg, patients with stable and continuous care) and smaller sample. As we will be able to collect up to 18 months of data, we will subset the relevant patient subpopulations within clinics in 6-month increments and model time as a between-subjects effect in the model described above to evaluate the effectiveness for each outcome. More specifically, we will add time (6, 12, and 18 months) and the product of time and arm that represents their interaction in level 2 of the model. We will then calculate the population-averaged marginal proportions and associated 95% CIs by arm and time points, along with the marginal effects between arms within time points and between arms across pairs of time points (ie, differences-in-differences). Significant marginal effects between arms across time would suggest a differential change between the arms across time. As all secondary CQM outcomes (Textbox 1) are also binary, we will use the same approach to evaluate between-arm differences on these outcomes as for the primary outcomes.

Intent-to-treat analyses will be used to establish effectiveness at the population level and per-protocol analyses to assess the impact of the tools when used. For the primary analysis, depending on the size of the intraclass correlation (between 0.01 to 0.05), this study has at least 80% power to detect a 9%-17% difference in blood pressure control (n=343 per CHC; assuming baseline level of 60% blood pressure control calculated from OCHIN data) and a 10%-18% difference in HbA_1c_ control (n=214 per CHC; assuming baseline level of 34% HbA_1c_ control calculated from OCHIN data) between the intervention and control groups at a two-tailed α level of .05.

Primary and secondary analysis variables.

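### The log link for the binary primary outcomes does not keep probabilities below 1, and its one benefit, a direct risk ratio, is not reported; a logit link gives the same planned results

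*Protocol article*

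**What the plan says.** Protocol article, Quantitative Analyses, sets a two-level model for blood pressure control and HbA1c control: "the generalized form of the hierarchical linear model with a log link and binomial distribution will be used". Level one holds person-level covariates, of which "this list will be finalized based on the extent to which person-level covariates were balanced between the final intervention and control arms". The candidates in the textbox of analysis variables include age, number of visits, a comorbidity score and provider panel size. Level two holds arm and a random CHC intercept, whose distribution is not named.

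The results to be reported are on the probability scale: "Population-averaged marginal proportions and associated 95% CIs will be calculated by arm, along with the difference between those proportions". No risk ratio is planned. The time-by-arm analysis and the secondary outcomes use the same model.

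The rates come from the power statement in the same section. For blood pressure it gives "n=343 per CHC; assuming baseline level of 60% blood pressure control calculated from OCHIN data" and says that "this study has at least 80% power to detect a 9%-17% difference in blood pressure control", over an ICC of 0.01 to 0.05. For HbA1c the baseline is 34%, with 214 patients per CHC and a detectable difference of 10% to 18%.

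**The concern.** Under a log link the probability is the exponential of the linear predictor, so the predictor must stay at or below zero. A random intercept with the usual normal distribution has no upper limit, and neither does the contribution of an uncategorized covariate such as visit count. When the outcome is common, zero is close: at 77%, any combined multiplier above 1/0.77 = 1.30 gives a probability above 1.

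Two things are at stake. The fit may stop at the boundary or not converge. And because the population-averaged proportions are to incorporate the random effects, the averaging can run over a region where the model's probabilities are impossible. The usual reason to accept this is a coefficient that reads directly as a risk ratio, and this plan does not report one.

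**Working it through.** **Inputs.** Blood pressure baseline 60%, 343 patients per CHC; HbA1c baseline 34%, 214 per CHC; ICC 0.01 to 0.05; detectable differences 9 to 17 and 10 to 18 points (all from Quantitative Analyses). Clinics: 6 intervention and 30 control (Randomization and Recruitment). Assumed here: a normal CHC intercept and the size of the covariate effects.

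**Where the rates come from.** Adding the stated differences to baseline gives 69% to 77% for blood pressure and 44% to 52% for HbA1c in the intervention arm. I tried to reproduce those differences with the design effect 1 + (m − 1) × ICC, two-sided α of 0.05 and 80% power. For blood pressure the design effect is 4.42 at ICC 0.01 and 18.1 at ICC 0.05. With 6 versus 30 clinics the detectable differences are 6.9 to 13.6 points for blood pressure and 7.3 to 14.2 for HbA1c. The stated figures are matched closely by 6 versus 6 clinics (8.8 to 17.2 and 9.5 to 18.6). The claim of at least 80% power is therefore true but conservative. That is a separate matter; here it only means that 77% is the top of the plan's own range.

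**Share of clinics above 1, intercept only.** Choose the log-scale variance so that the between-CHC variance equals ICC × p(1 − p):

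s² = ln(1 + ICC × (1 − p)/p), and P(probability > 1) = 1 − Φ((−ln p + s²/2)/s).

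At ICC 0.05:

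| p | s² | s | (−ln p + s²/2)/s | P(> 1) |
|---|---|---|---|---|
| 0.60 | 0.0328 | 0.181 | 0.527/0.181 = 2.91 | 0.2% |
| 0.69 | 0.0222 | 0.149 | 0.382/0.149 = 2.56 | 0.5% |
| 0.77 | 0.0148 | 0.122 | 0.269/0.122 = 2.21 | 1.4% |

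If the 6 intervention clinics were at 77%, the chance that at least one exceeds 1 would be 1 − (1 − 0.0136)^6 = 8%. At ICC 0.01 all three shares are about zero. For HbA1c at 52% and ICC 0.05 the share is 0.07%. Rates for the secondary outcomes are not given; at an assumed 85% or 90%, ICC 0.05 gives 3.7% and 7.3%.

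**Share of patients above 1, with covariates.** Add an assumed covariate variance of 0.15² or 0.25² to s² in the same formula, at ICC 0.05:

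- p = 0.60: s² = 0.0328 + 0.0225 = 0.0553 gives 1.1%; s² = 0.0328 + 0.0625 = 0.0953 gives 3.5%.
- p = 0.77: s² = 0.0148 + 0.0225 = 0.0373 gives 7.4%; s² = 0.0148 + 0.0625 = 0.0773 gives 14.0%.

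**Fitting.** Data were simulated from a logit model with 36 clinics at the planned sizes and four person-level covariates. Log-odds coefficients were 0.10 to 0.15 (weak) or 0.3 in absolute value (moderate). Each outcome was run at two settings: ICC 0.01 with the smaller stated difference and ICC 0.05 with the larger, 40 runs each. The fits below are log-link binomial GLMs without a random intercept.

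| Outcome, covariates | Failed (ICC 0.01; 0.05) | Fitted value at or above the boundary |
|---|---|---|
| Blood pressure, weak | 0/40; 0/40 | 13/80 |
| Blood pressure, moderate | 11/40; 7/40 | 79/80 |
| HbA1c, weak | 0/40; 2/40 | 2/80 |
| HbA1c, moderate | 16/40; 13/40 | 78/80 |

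The logit GLM converged in 320/320 fits. A further set of pooled blood pressure fits, without clinic effects, put log-link failure at about 3% to 17% with weak covariates and 13% to 40% with moderate to strong ones.

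The random-intercept model was fitted for blood pressure only, 8 runs per setting, with 15-point quadrature. With moderate covariates the log-link version converged in 1/8 runs (ICC 0.01) and 0/8 (ICC 0.05); without covariates it converged in 8/8 at each. The logit version converged in 32/32. These runs are few and the quadrature is coarse, so they indicate direction only.

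**The case against.** The case for leaving the model alone has real content.

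- **A log link has a merit here.** A clinic effect multiplies both arms by the same factor, so the conditional and population-averaged risk ratios for arm coincide, which odds ratios do not do. This is true, but the plan reports no risk ratio and obtains its population-averaged results by a separate calculation.
- **The exposure is uneven.** The 77% is baseline plus the largest detectable difference, not an expected rate, and would apply to 6 of 36 clinics. Control clinics sit near 60%, and HbA1c control is lower still. This stands and limits the size of the point.
- **Covariates drive most of the trouble, and they are not settled.** Neither the final list nor their form or effects are given, and categorized covariates would be bounded. The simulated data came from a logit model, so the log-link model was misspecified by construction. This stands: the failure rates are conditional on assumptions.
- **Log may be a slip for logit.** Then the fitting problems vanish, but the published primary model is misstated and still needs correcting.

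A reader might also infer that the plan has no fallback if the model fails, so that an unplanned change after seeing the data is inevitable. The document does not support that: this is a condensed article, the analysis plan is not shown, and convergence handling commonly belongs there.

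**Conclusion.** The point holds as a poorly chosen link, stated explicitly, for outcomes that include one at about 60% or higher. The absence of an upper bound follows from the link itself. So does the absence of an offsetting benefit, given what the plan reports.

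Its practical size is uncertain. From the clinic intercept alone it is small: at most 1.4% of clinics at the top of the blood pressure range with ICC 0.05, and about nil at ICC 0.01. With covariates it can matter: 7% to 14% of patients at 77%, and frequent boundary fits or failures when effects are moderate. These figures rest on a normal intercept, which the article implies but does not state, and on assumed covariate effects.

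A reader might conclude that the primary analyses will fail or that their intervals will be wrong. The evidence does not go that far: with weak covariates most fits converged, and without covariates the random-intercept log-link model converged in every run.

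**What to change.** Specify a logit link with the binomial distribution and the CHC random intercept for the primary outcomes, the time-by-arm analysis and the secondary outcomes. Obtain the population-averaged proportions by arm, their difference and the intervals by marginal standardization, averaging over the covariates and the random-effect distribution, as the plan already intends. If log was written for logit, correct the word. If the log link is deliberate, state the reason and how probabilities are kept at or below 1.

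The cost is one word in the model specification; the reported quantities do not change. The downside is that the arm coefficient becomes an odds ratio rather than a risk ratio, but the plan reports neither.

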### Objectives

This paper describes the protocol for a National Institutes of Health (NIH)-funded study (COHERE; Contextualized Care in Community Health Centers’ Electronic Health Records; R01MD014886) designed to develop and test CDS tools that present care team members with a given patient’s social risk information and both recommend and facilitate care plan adaptations based on those risks. This study will test the hypothesis that providing CDS that alerts care team members to patients’ known social risks and recommends relevant care plan adaptations will result in improved health outcomes. This study’s focus is on hypertension and diabetes control; however, the results will have implications for a wide range of morbidities.

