#### Main Trial

Intervention clinics will have the CDS tools turned on in their EHR and will be followed for 18 months to assess (1) tool adoption, (2) the extent to which tool suggestions are enacted by care team members, and (3) the impact of tool use on two national clinical quality measures (CQMs) [41]: blood pressure control and hemoglobin A_1c_ (HbA_1c_) control. We will also assess care team members’ perceptions of the tools’ usability and impacts on care quality and patient-provider interactions.

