### Randomization and Recruitment

All OCHIN clinics that provide primary care and have documented ≥200 social risk screenings (excluding the pilot clinics) will be identified. It is anticipated that approximately 60 clinics will meet these criteria. Eligible clinics will be randomized 1:1 to 1 of 2 groups: potential intervention or control. Clinics from the potential intervention group (n=30) will be recruited in random order until 6 agree to participate. In the study analyses, outcomes in these 6 intervention clinics will be compared with those in the control clinics (n=30). This approach allows for randomization between the intervention and control arms while eliminating the recruitment of CHCs to a study where some will receive no intervention (ie, only clinics that will receive the intervention will be contacted for recruitment). This method is possible as all OCHIN member CHCs agree that their EHR data may be used in research as part of their membership agreement.

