**Potential covariates**
Patient covariates: Age, gender, race and ethnicity, primary language, poverty level, insurance status at a visit, and number of visits to that site or provider in last year (care use)Patient comorbidities: Charlson comorbidity score (modified)—an indicator of serious comorbid conditions that may shorten life expectancyVisit type:In-person, telephone, and virtualOutreach, encounterProvider type:Degree (eg, medical doctor, registered nurse, or physician assistant)Prescribing privileges (yes or no)Number of patients in panel

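### Primary-model covariates are to be chosen by observed balance between the arms, from a pool not limited to values before tool activation

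*Protocol article*

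**What the plan says.** The article, under Quantitative Analyses, specifies a two-level model for the two primary outcomes. Person-level covariates sit at level 1. Level 2, the clinic level, "will include arm as an independent variable (control vs intervention) and a random effect for the intercept". On the covariates it says "Textbox 1 shows other potential covariates" and then "this list will be finalized based on the extent to which person-level covariates were balanced between the final intervention and control arms". It gives no threshold for imbalance and no set that is included regardless.

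The pool in Textbox 1 (Potential covariates) holds patient characteristics and a modified Charlson score. It also holds "insurance status at a visit, and number of visits to that site or provider in last year (care use", visit type (mode of contact, and outreach or encounter) and provider characteristics. It contains no clinic-level value of the outcome measures before activation.

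Three other statements bear on timing and arms:

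- Patients enter a measure's denominator when "eligible for that measure at the time of a clinic visit" (Quantitative Analyses).
- Intervention clinics have the tools turned on and "will be followed for 18 months to assess" adoption and impact (Main Trial).
- For the analysis, "outcomes in these 6 intervention clinics will be compared with those in the control clinics (n=30" (Randomization and Recruitment). The 6 are those that agreed among the 30 randomized to the potential intervention group.

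**The concern.** Two features of the stated rule work against the primary comparison.

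First, the criterion is the difference between arms, not the strength of association with the outcome. A covariate that predicts control strongly but happens to be balanced is left out, and its variance stays in the residual. A weak predictor that happens to be unbalanced is put in. With no threshold stated, the primary model stays open until the arms have been compared.

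Second, the rule cannot distinguish a difference that existed before activation from one that the tools produced. The tools are meant to "recommend and facilitate care plan adaptations based on those risks", and transportation insecurity is among the social risks named in the abstract and Background. A change in how or how often a patient is seen is a plausible adaptation. Such a change would show as imbalance in visit type or visit count, and the rule would then point to exactly those variables for adjustment. At stake is part of the effect the trial is meant to estimate, along with precision in a design with only 6 intervention clinics.

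**Working it through.** The article attaches no figure to the covariate rule, so there is none to reproduce. Inputs from the article: 6 and 30 clinics (Randomization and Recruitment); ICC 0.01 to 0.05; 343 patients per clinic for blood pressure (BP) and 214 for HbA1c; stated differences of 9 to 17 points for BP (Quantitative Analyses). Everything else below is marked as an assumption.

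**1. How far chance decides what enters.** For clinics drawn at random, the standardized difference in one covariate has SD = √[(1/30 + 1/6) × (ρ + (1−ρ)/343)], where ρ is that covariate's own ICC (assumed). For ρ = 0.01, 0.05 and 0.10 the SD is 0.051, 0.103 and 0.143. With an assumed cut-off of 0.1, the chance of being called unbalanced is 5%, 33% and 49%. This is before any effect of which clinics consent.

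**2. Balance selection against a fixed set.** Clinic-level simulation with no true effect and 8,000 runs. Assumptions: 7 baseline covariates, jointly explaining R² of the clinic-level outcome variance; a covariate is selected if its arm difference exceeds 0.45 or 0.88 clinic SD. Since √(1/30 + 1/6) = 0.447, these cut-offs are about one and two standard errors. The SE is the empirical SD of the estimate.

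| R² | Cut-off | Type I, fixed set | Type I, selected | SE, fixed set | SE, selected | Ratio of SEs |
|---|---|---|---|---|---|---|
| 0.3 | 0.45 | 5.1% | 3.5% | 0.421 | 0.428 | 1.02 |
| 0.3 | 0.88 | 4.6% | 4.2% | 0.415 | 0.438 | 1.06 |
| 0.6 | 0.45 | 4.7% | 2.0% | 0.315 | 0.363 | 1.15 |
| 0.6 | 0.88 | 5.0% | 3.4% | 0.319 | 0.421 | 1.32 |

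Mean estimates under selection lie between −0.008 and 0.007, which is zero within simulation error. Selection by balance is therefore conservative and less precise here, but not biased.

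**3. Timing of the visit count.** If the one-year look-back is indexed to a visit at month t after activation, the share of the window after activation is min(t, 12)/12. That is one half at month 6 and all of it from month 12. If it is indexed to activation, the share is zero. The article gives no index date.

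**4. Effect removed by adjusting for a changed visit variable.** Amount removed = a × b, where a is the shift the tools cause in the variable and b is the difference in control associated with it. Both are assumptions.

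| a | b | Removed | Share of 9 points | Share of 17 points |
|---|---|---|---|---|
| 0 | any | 0 | 0% | 0% |
| 0.05 | 0.05 | 0.25 points | 3% | 1.5% |
| 0.10 | 0.10 | 1 point | 11% | 6% |
| 0.20 | 0.20 | 4 points | 44% | 24% |

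**5. Gain from the clinic's pre-activation level.** Assume clinic autocorrelation π and a pre-activation sample of the same size from different patients. Then r = π × m·ICC / (1 + (m−1)·ICC), and the SE is multiplied by √(1−r²).

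| Outcome | ICC | m·ICC / (1+(m−1)·ICC) | SE factor, π = 0.5 | SE factor, π = 0.8 |
|---|---|---|---|---|
| BP, m = 343 | 0.01 | 3.43/4.42 = 0.776 | 0.92 | 0.78 |
| BP, m = 343 | 0.05 | 17.15/18.10 = 0.948 | 0.88 | 0.65 |
| HbA1c, m = 214 | 0.01 | 2.14/3.13 = 0.684 | 0.94 | 0.84 |
| HbA1c, m = 214 | 0.05 | 10.70/11.65 = 0.918 | 0.89 | 0.68 |

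For BP the reduction is 8-12% at π = 0.5 and 22-35% at π = 0.8. For HbA1c it is 6-11% and 16-32%. The article does not give π.

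**The case against.** The strongest reply is that nothing is committed. The article calls these potential covariates, so visit type and visit count may never enter. No section says that the tools change visit mode or count. The adaptations given as examples in the Background concern medication storage and insulin dosing, and the tools' content was still to be decided in the formative phase. The model has person and clinic levels but no visit level, so each covariate must be reduced to one value per person, and a value from before activation fits the text as well as a later one. The final arms can also be read as those formed once 6 clinics have agreed, which could precede activation. Because those 6 consented while the controls were never asked, adjusting for differences has a real confounding rationale. Finally, an analysis plan that is not shown may settle the list.

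Most of this stands, and it rules out the stronger reading that the primary estimate is adjusted for mediators or is a direct effect. A reader might infer that from the pool, but the documents do not establish it. Nor do they show that the list will be left open until outcome data have been seen.

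The reply does not remove the rule itself. The article states positively that balance between the arms decides the list, and it sets no pre-activation limit on the candidates. An analysis plan that followed the article would carry both features forward. The confounding rationale supports adjustment, but not choosing the adjustment set by observed balance.

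**Conclusion.** The concern holds in a limited form. The article fixes a balance-based selection rule for the primary model and applies it to a pool that may contain values arising after activation. By itself the rule costs precision (SE 2% to 32% larger in the illustration) and makes the nominal error rate inexact in the conservative direction (2.0%-4.2% in place of 5%). Those figures depend on the 7 assumed covariates, their R² and the cut-offs. A reader might infer bias or an inflated false-positive rate; the illustration shows neither.

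The more serious consequence is conditional. If the tools alter visit mode or frequency, the rule favours adjusting for that alteration and could remove up to 4 points over the assumed range, or nothing if visits are unaffected. No particular mediated share can be drawn from the documents.

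The absence of a clinic-level baseline from a provisional list is not an error in itself. It belongs in the remedy because the article describes the primary outcomes as changes in the quality measures, and because it is likely to help with 6 intervention clinics, by an amount that depends on the unknown autocorrelation.

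**What to change.** Before activation, replace the balance rule with a fixed list chosen on prognostic grounds from the patient variables in Textbox 1: age, gender, language, race and ethnicity, insurance, poverty level, modified Charlson score, and visits in the year before activation. Measure all of them at or before activation. Add the clinic's pre-activation level of the relevant quality measure at level 2. Leave visit type and follow-up visit counts out of the effectiveness model and report them by arm as process outcomes. Adjustment for differences between the 6 consenting clinics and the controls is thereby kept.

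The cost is wording: quantitative data already come from one centrally managed EHR. The clinic baseline uses one clinic-level degree of freedom (36 − 3 = 33 in place of 36 − 2 = 34). A fixed list also gives less freedom to respond to an unexpected imbalance; a sensitivity analysis that adds unbalanced pre-activation covariates covers that.

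### The primary outcomes are called changes, but no pre-activation outcome enters either model, so any baseline gap between agreeing and control clinics stays unadjusted and the differences-in-differences have no baseline

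*Protocol article*

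**What the plan says.** Under Quantitative Analyses the protocol article states: "The primary trial outcomes are changes in the two CQMs" for blood pressure and HbA1c. The model described next has person-level covariates at level 1. The clinic level "will include arm as an independent variable (control vs intervention) and a random effect for the intercept". Its output is a marginal proportion for each arm, "along with the difference between those proportions (ie, the marginal effect".

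The candidate covariates in Textbox 1 start with "Age, gender, race and ethnicity, primary language, poverty level, insurance status at a visit, and number of visits to that site" and go on to comorbidity, visit type and provider characteristics. No earlier value of either outcome is listed, for the patient or for the clinic. On selection, "this list will be finalized based on the extent to which person-level covariates were balanced" between the arms.

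For the secondary analysis, "we will add time (6, 12, and 18 months) and the product of time and arm" go into level 2. Arms are compared within each time point and also "between arms across pairs of time points (ie, differences-in-differences".

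Three further facts matter:
- **Randomization and Recruitment:** 30 clinics are allocated to each group. Those in the potential intervention group are approached in random order until 6 agree. All 30 control clinics are analysed without being approached. EHR data from every member clinic may be used for research.
- **Main Trial and Results:** follow-up with the tools on lasts 18 months, December 2022 to May 2024.
- **Power statement:** ICC 0.01 to 0.05; 343 patients per clinic at 60% for blood pressure; 214 per clinic at 34% for HbA1c.

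**The concern.** A change needs a starting value, and neither model has one. The primary contrast compares levels after activation. Even if earlier records were in the data set, the model has no time term to separate them.

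Two things are at stake. First, the intervention arm consists of clinics that said yes, and the control arm of all clinics allocated to it. If willing clinics already control blood pressure or HbA1c better or worse, the primary contrast includes that gap. A random intercept does not remove a systematic gap between arms, and person-level covariates need not. Second, the secondary analysis is meant to show differential change, but it can show only change from one post-activation period to another.

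**Working it through.** **1. The plan's own detectable difference.** Take d = (1.96 + 0.84) × SE, with SE² = DE × [p₁(1−p₁)/(6m) + p₀(1−p₀)/(30m)] and DE = 1 + (m−1) × ICC. For blood pressure at ICC 0.05, DE = 1 + 342 × 0.05 = 18.1. At p₁ = 0.730, SE² = 0.730 × 0.270 × 18.1/2058 + 0.24 × 18.1/10290 = 0.00173 + 0.00042, so SE = 0.0464 and d = 13.0 points. At ICC 0.01, DE = 4.42 and d = 6.75 (about 6.8). HbA1c gives 7.4 to 14.5. The stated 9 to 17 and 10 to 18 points are not reproduced for 6 v 30 clinics; 6 v 6 comes close (8.8 to 17.0 and 9.5 to 18.4). That is a separate matter, since at least 80% power remains true as worded. The present point does not rest on it.

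**2. Is there a month 0?** December 2022 (1 month) + 2023 (12) + January to May 2024 (5) = 18 months. Three 6-month increments use all 18, so every time point lies after activation.

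**3. What each contrast returns**, without sampling noise, in points. Gaps and effects are illustrative assumptions.

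| Scenario | Primary contrast | Planned differences-in-differences (6→12, 12→18, 6→18) | Against a baseline (6, 12, 18) |
|---|---|---|---|
| No gap, constant effect 9 | 9 | 0, 0, 0 | 9, 9, 9 |
| Gap 5, no effect | 5 | 0, 0, 0 | 0, 0, 0 |
| Gap 5, constant effect 9 | 14 | 0, 0, 0 | 9, 9, 9 |
| No gap, effect 3, 6, 9 | 6 | 3, 3, 6 | 3, 6, 9 |

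**4. Chance differences between clinics.** Clinic SD = √(ICC × p(1−p)). The SD of the arm difference is clinic SD × √(1/6 + 1/30) = clinic SD × 0.447. For blood pressure at ICC 0.05: √(0.05 × 0.24) = 11.0 points, × 0.447 = 4.9. At ICC 0.01: 4.9 × 0.447 = 2.2. For HbA1c the range is 2.1 to 4.7. The random intercept carries this variation into the standard error.

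**5. Precision gained from a baseline.** The correlation of clinic means is r = CAC × m·ICC/(1 + (m−1)·ICC), where CAC is the clinic autocorrelation between periods. The article gives no CAC, so 0.4 to 0.8 is assumed, with 343 patients per clinic in the earlier period too. The ratio is 17.15/18.1 = 0.948 at ICC 0.05 and 3.43/4.42 = 0.776 at ICC 0.01. Covariate adjustment multiplies d by √(1−r²); a plain post-minus-pre contrast multiplies it by √(2(1−r)).

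| ICC | No baseline | CAC | r | Covariate-adjusted | Post minus pre |
|---|---|---|---|---|---|
| 0.05 | 13.0 | 0.4 | 0.379 | 12.0 | 14.5 |
| 0.05 | 13.0 | 0.6 | 0.569 | 10.7 | 12.1 |
| 0.05 | 13.0 | 0.8 | 0.758 | 8.5 | 9.1 |
| 0.01 | 6.8 | 0.4 | 0.310 | 6.4 | 7.9 |
| 0.01 | 6.8 | 0.6 | 0.466 | 6.0 | 7.0 |
| 0.01 | 6.8 | 0.8 | 0.621 | 5.3 | 5.9 |

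Post minus pre loses precision when r < 0.5, that is, when CAC is below 0.5/0.948 = 0.53 (ICC 0.05) or 0.5/0.776 = 0.64 (ICC 0.01).

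**6. What adjustment leaves behind.** If the slope on the earlier proportion equals r (equal variances in both periods), a stable 5-point gap leaves 5 × (1−r). At ICC 0.05 that is 5 × 0.242 = 1.2 points at CAC 0.8 and 5 × 0.621 = 3.1 at CAC 0.4.

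**The case against.** The best defence is that change is loose wording. Textbox 1 lists the outcomes as binary status, the power statement concerns a difference between groups, and the model delivers exactly that. Comparing randomized clusters after the intervention only is an accepted design, and baseline adjustment is then a matter of efficiency. This would largely answer the point if the analysed clinics were the randomized ones. They are 6 agreeing clinics out of 30 against all 30 controls, so the argument does not carry over in full. It does stand to this extent: if nearly every clinic approached agrees, the arm is close to a random sample and the gap is likely to be small.

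A reader might infer that ordinary baseline differences between clinics are read as effect. The article does not support that: its interval allows for differences between clinics, so the 2.2 to 4.9 points are noise already counted and do not measure bias.

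A reader might also infer that the plan cannot detect an effect that starts at activation. It can. The primary contrast and the within-time-point contrasts would both show it. A zero in the planned differences-in-differences is a correct answer about trend from month 6 to month 18; the error would be to read it as no benefit.

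The article's objection to a panel of patients does not block a baseline, because an earlier cross-section per clinic needs no repeated patients. Nor is this detail left to an analysis plan: the article itself fixes the model terms, time points and contrasts.

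**Conclusion.** The point holds in this form. The named outcome (change) and the primary model (level after activation) disagree, and no pre-activation outcome enters either model. The number of visits in the last year may reach back before activation, but it is not an outcome. The risk of bias is confined to a systematic gap from the agreement step. The documents give no basis for its size, and any such gap passes point for point into the primary and within-time-point contrasts. The differences-in-differences are blind to an effect complete in the first 6 months and constant after, but they do see later growth.

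The gain in precision is real but uncertain. At ICC 0.05 the detectable blood pressure difference falls from 13.0 to 12.0, 10.7 or 8.5 points, and at ICC 0.01 from 6.8 to 6.4, 6.0 or 5.3, for an assumed autocorrelation of 0.4, 0.6 or 0.8. No single value in that range should be quoted as the benefit.

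**What to change.** - Extract the same two measures for all 36 analysed clinics over a pre-activation period, for example the 6 or 12 months before December 2022, with the same restriction to patients with known social risks.
- Add each clinic's pre-activation proportion as a level-2 covariate in the primary model, and reword the outcome as the arm difference in control after activation, adjusted for clinic baseline.
- Add a baseline time point to the secondary model and form each differences-in-differences contrast against it. Describe contrasts among months 6, 12 and 18 as trend after activation.
- Prefer covariate adjustment for the primary analysis, because a plain post-minus-pre contrast can lose precision. The secondary contrast against baseline complements it, since it removes in full a gap that is stable over time.
- Report how many clinics were approached to obtain 6, and the pre-activation proportions by arm.

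The cost is revised wording, one more extract from a centrally managed database, and one level-2 degree of freedom (34 to 33 with 36 clinics). No sites or patients are added. Two limits remain. Earlier denominators of patients with known social risks may fall short of 343 and 214 per clinic, since eligibility requires only 200 documented screenings, and this would reduce the gain. Adjustment may also remove only part of the selection from the agreement step.
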